## Abstract

**Background:**

Decades of research and practice experience have led to an extensive body of evidence about effective home safety modifications. However, the benefits of safety modifications have not reached all segments of society. Poor quality housing in low-income neighborhoods, along with limited access to safety products and injury prevention information, can be significant barriers to child safety.

**Methods:**

This is a longitudinal study of 300 low-income families in Baltimore City and Baltimore County with children under 7 years of age who are referred from existing Green & Healthy Homes Initiative (GHHI) home visiting programs. Three home visits will be completed to assess home injury hazards using a previously developed tool, the Children’s Housing Assessment for a Safe Environment (CHASE), and provide a Scope of Work that includes home modifications specific to the identified home injury hazards. An Assessor will also provide do-it-yourself education materials and injury prevention supplies to assist residents in completing the modifications. If the parent or caregiver is unable to complete the home modifications, a professional Housing Intervention Services team will complete the home modifications necessary to prevent injury in the home. This study will involve both quantitative and qualitative data analysis methods. Paired and regression analyses will be conducted to examine the maintenance of modifications and the variables associated with positive outcomes. A thematic analysis of staff and participant interviews will be used to identify perceived barriers and facilitators of successful program implementation.

**Discussion:**

Better data on residential injuries of children and an improvement in the overall surveillance of home injuries are necessitated. This study will set a strong foundation for a larger future study of health and cost effectiveness outcomes and will advance our understanding of the feasibility, costs, and potential benefits of addressing and preventing home injuries to children.

## Background

Unintentional injuries are the leading cause of death in children in the US, resulting in 12,000 deaths and 9.2 million emergency department visits each year (Centers for Disease Control and Prevention 2021). Children are especially at risk of injury in the home, with home-related injuries such as poisoning, suffocation, and drowning contributing substantially to injury-related death in this age group; an estimated 3,100 deaths occur annually due to home injury in children aged 14 and under alone (Centers for Disease Control and Prevention 2021; Centers for Disease Control and Prevention 2023). For every death, there are almost 1600 nonfatal home injuries, too many of which lead to lifelong disability or reduced quality of life for children and their families (National Safety Council 2023). Adding to these tragedies is that many of these injuries are preventable with proven and relatively simple home modifications (Turner et al. 2011).

Low-income and certain minority populations are disproportionately affected by child injuries, though racial disparities seen in injury rates can be attributed to living in dangerous environments with greater risk for injury and a host of social disparities rather than race or ethnicity (National Safety Council. 2023; Shenassa et al. 2017; Fallat et al. 2006; Bernard et al. 2007; Kendrick et al. 2009). Housing conditions in low-income neighborhoods likely contribute to low-income families’ increased risk for home injury for children and adults alike (Bishai et al. 2002; Reading et al. 2017; Lyons et al. 2006; Haynes et al. 2003; Reimers and Laflamme 2005). Residents of all ages living in substandard housing are at increased risk for fire, electrical injuries, lead poisoning, falls, and other injuries. Several studies have found that children living in socioeconomically disadvantaged neighborhoods are at increased risk of injury, even after accounting for individual-level factors (Reading et al. 2017; Haynes et al. 2003; Durkin et al. 1994; O’Campo et al. 2000; Parker et al. 2017).

Previous research on modifications to low-income housing has demonstrated that home modification interventions can reduce injury (Turner et al. 2011). A widely cited example of successfully modifying housing conditions to reduce child injury is New York City’s “Children Can’t Fly” program (Spiegel and Lindaman 1995), which installed window guards on high-rise apartments and is credited with significant reduction in morbidity and mortality due to falls from windows. The success of the program resulted in legislation requiring landlords to install window guards. Studies of smoke alarm canvassing and installation programs provide another successful example of modifying the home environment to reduce home injury risk to children (Gielen et al. 2013; Ta et al. 2006; Ballesteros et al. 2005; Wintemute et al. 2014). A comprehensive, internationally representative Cochrane review of interventions to reduce in-home hazards in households with children found that seven of the eight studies observed either a reduction in hazards or an increase in the presence of safety features (fireguards, electric socket covers, cabinet locks, window safety, and hot water temperature) (Parker et al. 2017). Interventions involving home safety modifications align well with the Health Belief Model (HBM), which suggests that individuals’ attitudes and beliefs about health problems influence their health-related behaviors. For example, installation programs reduce families’ perceived barriers to maintaining safe housing by overcoming limitations to accessing the needed safety products and services.

In 1976, the US government recognized the need for formal housing hazard assessment tools when the Centers for Disease Control and Prevention (CDC) and the American Public Health Association issued the Basic Housing Inspection Manual (Centers for Disease Control and Prevention 2009). Since that time, additional housing assessment tools and programs have emerged including United States Department of Housing and Urban Development’s (HUD) Housing Quality Standards (HQS) and, in 2005, the launch of the Healthy Homes Initiative, which includes the Healthy Housing Inspection Manual. Despite this progress, the lack of a single validated and comprehensive housing hazard assessment tool has been identified as a major gap in the fight against housing-related health hazards. Although there are separate standardized tools for specific indoor environmental hazards, such as lead paint, asbestos, and radon, there is no standardized tool covering the many different injury risks in the home, such as fire hazards, fall hazards, and medicine storage (Jacobs 2006). A literature review of housing and children’s health calls for better data on residential injuries of children, particularly emphasizing the need for an improvement in the overall surveillance of home injuries (Hood 2005). A validated and comprehensive injury risk assessment tool, therefore, would be an important contribution and could be utilized in the future as a key part of a comprehensive home hazard assessment, and for better assessments of home injury risk for children specifically. The Children’s Housing Assessment for a Safe Environment (CHASE) tool is one such assessment that systematically identifies injury hazards. As described in a previous article, the CHASE tool demonstrated significantly greater likelihood of detecting hazards in the homes of injured children compared to HUD’s HQS tool while uniquely assessing risks that are hazardous to children, such as furniture tipping and medicine storage (Shields et al. 2020).

The study objectives are to: (1) implement injury prevention measures based on safety hazards identified using the CHASE tool within 300 low-income households (at or below 80% Area Median Income) in Baltimore City or County; (2) determine the costs of the injury prevention measures completed by residents and/or professional providers; and (3) conduct a formative evaluation to determine the feasibility of incorporating injury prevention into residential programs from the perspective of installers and residents, including identifying barriers and facilitators, and understand the consistency of implementing and maintaining the injury prevention measures by residents and staff.

## Methods

### Study design and setting

The CHASE Implementation Study will use quantitative and qualitative methods and a non-experimental design to estimate the magnitude of home injury risks, identify strategies for addressing those risks and sustaining those interventions, and calculate the costs of housing-related modifications to prevent childhood home injuries. The Johns Hopkins Institutional Review Board has approved this study protocol. The study will enroll clients from families living in Baltimore City or Baltimore County receiving housing services from Green & Healthy Homes Initiative (GHHI)’s home visiting programs. GHHI is a Baltimore-based non-profit organization that coordinates funding from government and private institutions to deliver cost-effective services that assess and remediate a range of home health hazards. GHHI and JHU have partnered over the past several years to increase the inclusion of injury risk identification and modification in existing GHHI programs.

Participating families will first receive two home visits from a housing assessor using the CHASE tool to identify injury hazards in the home, outline a workplan for remediation, and assess the short-term maintenance of home modifications. On a third visit, study data collectors will conduct the home assessment. During each home visit, the participant will complete a questionnaire and receive feedback with results from the home inspection.

### Theoretical grounding

The foundation of the CHASE Implementation Study is grounded in the Health Belief Model (HBM), which suggests that individuals are most likely to change their behavior if they believe: (1) that they are at risk of a serious condition and (2) that making the recommended change will prevent them from acquiring that condition. The HBM was selected due to its focus on perceived risk and self-efficacy and because most of the items on the CHASE assessment can be addressed at the individual level, making the HBM an appropriate model. Of the six constructs of the HBM—perceived susceptibility, severity, benefits, and barriers; self-efficacy; and cues to action—the study team focused on five: perceived susceptibility, severity (combined to perceived risk), self-efficacy, and cues to action. We did not include content about barriers and benefits because those are addressed by the home modifications included project participation and in the interest of having the family feedback form being as concise as possible.

### Measures

#### Baseline measures

The baseline interview will be conducted over the phone and will document household and participant sociodemographic characteristics, home characteristics, and measures of housing stability.

#### CHASE Home Assessment Form and Family Feedback Form

The CHASE tool is a 35-item home injury hazard assessment organized into 15 subdomains (e.g., carbon monoxide risks, falling furniture, and hot water burns). Each item on the CHASE tool assesses whether a household passes or fails to address a household hazard, offers facts about the hazard, and gives user-friendly, nationally accepted best practices and information on how to remediate the hazards to make homes safer. For example, the medicine storage subdomain includes the item, “All prescription and over-the-counter medicines have childproof caps,” with the response options, “Yes” or “No.” For this project, the CHASE tool was adapted into the CHASE Home Assessment Form, which includes all elements of the CHASE tool but further allows the housing assessor to specify home modifications needed to remediate the hazards during home inspections.

The Family Feedback Form is a companion form that uses information transferred from the CHASE Assessment Form to provide participants a short description of each home injury risk being assessed and why it is important, whether the home passed or failed each item and why, and next steps to be taken. In some instances, the form recommends calling a contractor for changes that the parent or caregiver cannot complete on their own. The Family Feedback Form will guide the educational intervention that will be delivered with the goal of preparing the parent or caregiver to initiate recommended changes. For example, on the topic of poison storage, the housing assessor will give the participant a lock box or cabinet locks and show them how to install it. Accordant with the HBM, these instructions are intended to increase the self-efficacy of the participant by showing them how to install and/or use a home safety product. The “Why This is Important” column of the Family Feedback Form also contains a perceived risk and/or an efficacy message that will be reiterated to the participant to reinforce the messages by a credible individual.

#### Health belief questionnaire

The Health Belief Questionnaire will measure perceived risk and self-efficacy which will be self -administered during all three home visits. The questionnaire consists of 17 questions that the participant will respond to on a 5-point Likert scale, ranging from “strongly agree” to “strongly disagree.” Sample questions include “I believe my child could get injured in my home” and “I have no idea how to make changes in my home to make it safer, such as installing cabinet locks or securing furniture.” Responses collected from the Health Belief Questionnaire will inform an understanding of the participants’ attitudes toward home hazards and making recommended changes, which will be examined for potential effects on the adoption and maintenance of safety modifications in the home.

#### Follow-up survey

Each time the home assessment is repeated, the Follow-up Survey will be administered to measure the time and cost to complete home modifications as well as collect via interview qualitative descriptions of the participants’ experiences with the assessment and modifications to better understand barriers and facilitators of the implementation of the recommended modifications.

### Procedures

The project is being conducted in three phases, the first of which has already been completed: (1) Convening a Community Advisory Committee (CAC); (2) CHASE tool implementation and observation; and (3) Qualitative interviews with implementers (See Fig. 1).

**Fig. 1 Fig1:**
[figure not shown]
Diagram of study flow

Phase 1 consisted of an initial convening of a CAC. CAC members were recruited from an existing Parent Advisory Board at the GHHI that offers feedback from family members. Parent Advisory Board members volunteered to participate and previously received program services from GHHI. We invited 11 Parent Advisory Board members to participate in the CAC. The CAC convened on August 23, 2021, with 6 members in attendance. CAC members were informed about the Implementation Study, reviewed key documents, and offered recommendations to ensure that those documents were clear and culturally appropriate for potential study participants. In advance of the meeting, CAC members were sent the oral consent form, Family Feedback Form, Mutual Service Agreement, and Follow-Up Questionnaire. Their ideas for revising and improving the documents were solicited at the meeting through a facilitated discussion. This process allowed the researchers to hear directly from CAC members and informed the subsequent changes that were made to those documents prior to use.

In Phase 1, educational fliers were also developed, including an overview flier that will be distributed to all participants during each home visit and topic-specific fliers for each of the injury hazards that homes could fail upon inspection using the CHASE Assessment Form. These fliers employ the HBM constructs to guide participants toward making suggested changes in their home. For example, if a participant’s water temperature registers above 120 degrees Fahrenheit, a flier on burn safety will be given stating that children have thinner skin than adults, which makes them more susceptible to burns from high water temperatures. Additionally, the researchers partnered with the creators of Make Safe Happen, a children’s home safety app, to help participants identify safety risks in their home and attain relevant products, such as a stair gate (McKenzie et al. 2018). A flier with the Make Safe Happen app information was developed to be provided to participants at the conclusion of the first home visit.

During Phase 2, 300 families will be enrolled. Parents or guardians (or emancipated minors who meet all other inclusion criteria)^1^ whose household is participating in a GHHI home visiting program will be invited to participate. Inclusion criteria include: (1) households with at least one child under 7 years of age or foster care families planning to host a child under 7; (2) the child under 7 years of age lives with the parent or legal guardian most of the time; (3) household income at or below 80% Area Median Income as defined by HUD; and (4) a home address in Baltimore City or Baltimore County.

While scheduling regular GHHI program visits, a GHHI Client Intake Specialist will use a project introduction script and eligibility screening form to briefly introduce the CHASE Implementation Study and review details, including a description of the project services and timeline, and determine if the parent or guardian is potentially interested and eligible to participate. Among those interested and eligible, the Client Intake Specialist will conduct the oral consent process, collect the baseline measures about the family, and schedule the first of three home visits, Home Visit 1 (HV1). Client intake specialist are bachelors trained as professionals whose roles requires customer service and project coordination skills.

HV1 will be scheduled within two weeks after intake. During HV1, a GHHI Assessor will visit the participant’s home, provide a copy of the completed consent form, and ask the study participant to complete a Health Belief Questionnaire. The Assessor will conduct a home inspection using the CHASE Home Assessment Form. After inspecting the residence, the Assessor will transfer assessment details onto the Family Feedback Form. Using this as a guide, the Assessor will then conduct a walk-through of the home providing advice and tailored education to assist caregivers in completing the identified home modifications or calling a contractor to do so on their own. The Assessor will also provide injury prevention supplies, a copy of the Family Feedback Form that lists the hazards identified in the home, and educational materials to assist the participants in completing the recommended modifications within 30 days. With the client’s consent, some photographs may be taken to document hazards identified during the housing assessment; no identifiable people or items will be captured in the phone. Participants may refuse without any negative repercussions.

Home Visit 2 (HV2) will occur approximately 30 days after HV1. A GHHI Assessor will return to reinspect the home, completing another CHASE Home Assessment Form to identify which hazardous item(s) the participants were able to modify on their own. They will complete a new Family Feedback Form to inform the family about the remaining risks in the home or to communicate that the home has passed all of the CHASE assessment items. A Research Assistant will administer the Health Belief Questionnaire and conduct a Follow-Up Survey.

For participants who were unable to address all hazards identified during HV1 (e.g., because the family could not or did not have sufficient means to address the hazards identified with home modifications alone or by calling a contractor), the Assessor will draft a Scope of Work for completion of the needed modifications and arrange a time to return to the home with the GHHI Housing Intervention Services Team, a professional home modification team who will complete the installation of any incomplete home modifications as described in the Scope of Work.^2^ When modifications are needed outside the capacity of the Housing Intervention Services team, GHHI will arrange for a contractor to complete the Scope of Work. All costs for modifications whether by the GHHI home modification team or by outside contractors will be paid for by the project with the grant funding. As is standard procedure for GHHI, there will be a post-intervention quality control assessment conducted by an Assessor immediately after the injury prevention intervention to verify that all measures on the Scope of Work were installed properly and meet HUD and project standards. Any discrepancies will be resolved. GHHI will document all costs, both labor and supplies, associated with completing the Scope of Work.

Home Visit 3 (HV3) will occur three months after all safety modifications have been completed. During HV3, a Research Assistant will complete the CHASE Home Assessment Form, the Health Belief Questionnaire, and a second Follow-Up Survey to assess the maintenance and effectiveness of the modifications. The Family Feedback Form will also be completed to inform families of any newly identified or persisting injury hazards, and informational resources will be provided to assist families in addressing identified risks. With the participant’s consent, additional photographs may be taken to demonstrate hazards identified as well as examples of successful repairs. These photographs will be used only for training purposes. We will make sure there are no identifiable people or items in the photographs. The participant can refuse to have photographs taken in their home.

The final phase of the study will involve qualitative interviews with those GHHI staff (Client Intake Specialist, Assessor, and Housing Intervention Services team) who are knowledgeable and experienced with the CHASE program to assess installer perspectives of feasibility, barriers, and facilitators to incorporating injury prevention measures into home visiting programs and sustaining those measures over time. GHHI will provide a list of staff involved in the project to the research team, and the study investigator will email each key informant to invite them to participate in a 30 min one-one-one interview.

### Sample size

A total of 300 homes (total of 900 home visits) will be studied in Baltimore City and Baltimore County, which will be referred from GHHI’s existing housing programs: Using a paired analysis of the number of hazards at Time 1 (HV1) versus Time 2 (HV3) with *N* = 300, *α* = 0.05, and assuming standard deviation 8.4 (Posner et al. 2004), we will have 80% power to detect a change in the mean number of hazards of 1.36.

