### Data analysis plan

Descriptive statistics and frequency tabulations will be generated on the number of hazards per home at each time point and the total time and cost per home for modifications. Pass scores for the home (number of items passed/total items) will be calculated as well as the prevalence of each individual hazard (out of *N* = 300). The mean, median, and range of costs per household and per injury prevention measure will be calculated. Homes with outliers for the number, duration, and cost of modifications will be identified and the characteristics associated with those homes will be noted. A paired analysis will be used to test the change in mean number of hazards present between HV1 and HV3. Additional analyses will be performed for individual hazards and modifications.

Maintenance of modifications is of particular interest, along with variables that are associated with higher rates of maintenance, which will be examined by comparing HV2 and HV3 data; this will be an analysis of proportion of modifications still in place at HV3 by outcome variable and by modification options. Frequency distributions for the additional variables of interest (sociodemographic characteristics, characteristics of the homes, participant knowledge, participant capacity to complete home modifications, participant satisfaction with the program, and perceived barriers and facilitators collected during the initial home visit by the Assessor) will be prepared. These variables will be used to conduct regression analyses to explain the hazard and maintenance outcomes described above as a function of referral source, sociodemographic characteristics, housing, knowledge, installer (homeowner/tenant and GHHI), and satisfaction. To explore the capacity of caregivers to install injury prevention measures, paired data from HV1 and HV2 will be used to compute change in mean number of hazards.

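### The stated 80% power for a 1.36-hazard change counts all 300 enrolled homes as complete HV1-HV3 pairs, and the article does not say what the SD of 8.4 measures

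*Protocol article*

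**What the plan says.** Methods, Procedures, sets the enrolment: "During Phase 2, 300 families will be enrolled". Methods, Sample size, then uses the same number twice. It counts visits without loss: "A total of 300 homes (total of 900 home visits) will be studied", which is three visits for each of 300 homes. It also takes 300 as the number of pairs: "Using a paired analysis of the number of hazards at Time 1 (HV1) versus Time 2 (HV3) with *N* = 300".

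The other inputs are α = 0.05, with sidedness not stated, and an SD introduced only as "assuming standard deviation 8.4", with a 2004 study cited. The result is that "we will have 80% power to detect a change in the mean number of hazards of 1.36".

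The matching analysis is in the Data analysis plan: "A paired analysis will be used to test the change in mean number of hazards present between HV1 and HV3". According to Procedures, HV2 falls about 30 days after HV1. Outstanding work is then done by the professional team or a contractor, and HV3 follows three months after all of it is complete.

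**The concern.** A paired test uses only homes measured at both visits. A home reaches HV3 after an initial visit, a reinspection, completion of any remaining work, and three further months. A home that withdraws, moves, or never has its work completed gives no pair. The power statement leaves no room for this: the number enrolled and the number of pairs analysed are the same.

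The paired formula also needs the SD of the within-home change. The article gives an SD without saying whether it describes the change or the count at a single visit, and it gives no HV1-HV3 correlation.

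This is the only quantitative justification of the sample size in the article. A reader would take 1.36 as what the study can detect. If pairs are lost and the SD of change really is 8.4, that is too favourable.

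**Working it through.** **Inputs.** From Sample size: 300 pairs, SD 8.4, α = 0.05, power 80%, detectable change 1.36. From Procedures: 300 enrolled. Assumed here, because the article gives neither: loss of 10%, 20% or 30% before HV3, and HV1-HV3 correlations r between 0 and 0.8.

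**1. Reproducing the plan's figure.** Detectable change = (z₀.₉₇₅ + z₀.₈₀) × SD of change / √n = (1.960 + 0.842) × 8.4 / √300 = 1.359, which rounds to the stated 1.36. Two-sided α is needed to obtain it; one-sided α would give 1.21. Power for 1.36 is Φ(1.36 × √300 / 8.4 − 1.960) = 80.1% (79.8% with the noncentral t).

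**2. Pairs required.** n = ((1.960 + 0.842) × 8.4 / 1.36)² = 299.4. So 300 complete pairs are needed, and 300 homes are enrolled.

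**3. Effect of loss, with 8.4 kept as the SD of change.** Power = Φ(1.36 × √n / 8.4 − 1.960).

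| Assumed loss | Pairs | Power for 1.36 | Change detectable with 80% power |
|---|---|---|---|
| 0% | 300 | 80.1% | 1.36 |
| 10% | 270 | 75.8% | 1.43 |
| 20% | 240 | 70.8% | 1.52 |
| 30% | 210 | 65.0% | 1.62 |

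With 240 pairs, the 95% confidence interval for the mean change has half-width 1.96 × 8.4 / √240 = 1.06.

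**4. Effect of what 8.4 measures, with 300 pairs.** If 8.4 is a single-visit SD, equal at both visits, then SD of change = 8.4 × √(2(1 − r)).

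| Assumed r | SD of change | Change detectable with 80% power |
|---|---|---|
| 0 | 11.88 | 1.92 |
| 0.5 | 8.40 | 1.36 |
| 0.8 | 5.31 | 0.86 |

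The stated 1.36 therefore follows if 8.4 is the SD of change, or if it is a single-visit SD with r = 0.5.

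**5. Both together, at 20% loss (240 pairs).** Power for 1.36 is 56.4% at r = 0.3, 70.8% at r = 0.5 and 89.9% at r = 0.7. Under the single-visit reading, the correlation can outweigh the loss in either direction.

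**The case against.** The strongest reply is that nothing has been miscalculated and the practical consequence is small. This is a non-experimental implementation study whose objectives concern implementation, cost and feasibility. The 300 households are written into its first objective, and no decision threshold depends on 1.36. At an assumed 20% loss the detectable change moves by 1.52 − 1.36 = 0.16 hazards. All of that stands, and it limits the weight of the point.

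A second reply is that a journal article may leave an attrition allowance to the full protocol. That would answer a complaint about a missing loss rate. It does not answer this one, because the article itself prints a power figure, and a count of 900 visits, that both require full retention. It is true that recording housing stability at baseline is not evidence of any particular rate of loss.

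Three stronger readings are tempting, and the article does not support them:

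- A reader might infer that the power claim stands or falls on 8.4 being the SD of change. Step 4 shows otherwise: a single-visit SD with r = 0.5 gives the same figure, and a higher correlation gives a better one. The article is silent on the meaning of 8.4 rather than contradictory. If remediation leaves few hazards at HV3, the SD of change would lie close to the HV1 SD, so 8.4 could be about right.
- A reader might infer that 8.4 is impossible for this outcome, given that "The CHASE tool is a 35-item home injury hazard assessment" and that remaining hazards are repaired at project expense. A normal change with mean 1.36 and SD 8.4 would have Φ(−1.36 / 8.4) = 44% of homes worsening. If no home worsened, the SD at that mean could not exceed √(1.36 × 33.64) = 6.76. But 1.36 is the smallest change detectable with 80% power, not a predicted change, and Procedures allows for newly identified hazards at HV3. A smaller SD would also mean more power: at 6.76, 210 pairs give Φ(1.36 × √210 / 6.76 − 1.960) = 83%.
- A reader might infer that 8.4 should be replaced by a value from earlier CHASE work. The Background describes that work only as a comparison of hazard detection with another tool, and no SD of change from it is shown.

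**Conclusion.** The point holds in a limited form. The 1.36 is arithmetically correct, but it equates enrolled homes with complete HV1-HV3 pairs, and the requirement of 299.4 pairs leaves no reserve. On the plan's own SD, taken as the SD of change, power falls to between 75.8% and 65.0% for losses of 10% to 30%. Those loss rates are assumptions.

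Separately, the article should say what 8.4 measures. Whether that ambiguity makes the plan optimistic or conservative cannot be settled from the article, so it does not show that the study is underpowered. What is shown is that the printed figure is conditional on full retention and on an undefined SD, and that the article states neither condition. This is a correction worth making to a published design figure, not a threat to the study.

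**What to change.** Keep 300 enrolled and rewrite the power sentence in Sample size.

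- State the expected number of homes completing both HV1 and HV3, and give the detectable change for that number. For example, at an assumed 20% loss, 240 complete pairs give 80% power for a mean change of 1.52 hazards, with a 95% confidence interval half-width of 1.06. The authors should substitute their own expected completion rate.
- Say in the same sentence that α is two-sided and that 8.4 is used as the SD of the HV1-HV3 change. If the cited value is a single-visit SD, show the detectable change over a range of correlations (with 300 pairs: 1.92 at r = 0, 1.36 at r = 0.5, 0.86 at r = 0.8), adjusted to the expected number of pairs.

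The cost is one paragraph and a slightly less favourable figure. No extra enrolment and no change to the analysis is needed.
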